**Method/design:**

All help seeking patients aged 14 to 35 years referred to the mental health services in three regions in the Netherlands are pre-screened with the Prodromal Questionnaire during a period of two years. Patients with a score of 18 or more on the sub-clinical positive symptoms items (45 items in total) will be assessed with the Comprehensive Assessment of At Risk Mental State (CAARMS). In a different pathway to care model all referrals from the mental health services in Amsterdam to the specialized psychosis clinic of the Academic Medical Centre in Amsterdam are also assessed with the CAARMS. The primary outcome is the transition rate to psychosis according to the CAARMS-criteria. Group differences will be analysed with chi-square tests and survival analyses.

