## Methods/Design

### Design

This study is a randomized controlled trial comparing treatment as usual (TAU) with an add-on cognitive behavioural therapy (CBT) targeted at the prevention of psychosis. The main outcome measure is the number of participants who develop florid psychosis within eighteen months. The secondary outcome is the reduction of the persistence of sub clinical symptoms.

The assessors are blinded to the research condition by not being able to check the patient status. The success of blinding is checked by having the assessors guess the presumed condition of the subject at each major assessment.

The design of this study has been approved by the Dutch Union of Medical-Ethics Trial Committees for mental health organizations. The trial will be conducted in compliance with the 'Declaration of Helsinki' (amendment of Edinburgh, 2000).

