### Randomisation

Randomisation will be stratified by site, to rule out factors concerning the institutions, therapists and habitat. The random allocation lists are generated by a web-based automated randomization system. To guarantee a numeric balance across conditions the randomisation will be performed separately for each research site, in random permuted blocks of ten. The allocation list will be kept in a remote secure location and an independent person randomly allocates the included patients. Patients are randomised after providing informed consent. The randomisation status is confirmed by fax to the randomisation bureau by the different sites.

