### Power calculation

We calculated power on an expected transition rate of 35 percent over eighteen months with a 50 percent reduction of transitions in the CBT-group. The sample we need for a 2-tailed test of the proportions with an alpha of .05 and a power of .80 is 2 × 93 for the reduction of the transition to psychosis and 2 × 82 for the persistence of ARMS and 2 × 91 for the transition into psychosis. A conservative estimate of the drop-out rate is twenty percent per year in schizophrenia research [24]. With an estimated 30 percent drop-out over 18 months, we decided to include 240 persons in the trial. Interventions to minimize drop-outs are flexibility to location of therapy (the appointment can be at their home-address or some times by telephone or webcam), sending Christmas- and Birthday cards every year. For the participants that end up in the CBT-treatment group there is also the possibility for web-cam therapy. All the participants that complete the study will have a financial compensation for expenses made.

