### Analyses

To determine baseline balance, several variables that are proven to be risk factors will be assessed, such as severity of ARMS-symptoms [43], heredity [44], growing up in a big city, stress and unhealthy behaviour of mother during pregnancy [45], migration and feelings of discrimination [35,36] and alcohol and drug use, including cannabis use [46]. If the baseline balance is disturbed, the analyses will be corrected for risk factors for transition to psychosis.

Missing data will be imputed by EM-algorithm. EM-algorithm recovers the complete factor loadings considerably better than simple imputation techniques [47,48].

Group differences will be analysed by unadjusted chi-square. Pearson's chi-square tests will be performed to analyse gender differences between the transition group and the non-transition group, Comparisons will be analysed on intention-to-treat, using the Statistical Package for the Social Sciences (SPSS for windows, version 17). Multiple logistic regression analyses will be used to explore which factors predict transition to psychosis within the UHR-group. To examine the effects of CBT on the positive symptoms reported on the first four scales of the CAARMS, analysis of co-variance will be used.

Survival analyses will be used to measure time to transition and risk factors for developing a first episode psychosis. We will conduct Kaplan-Meier curves to explore the cumulative probability of developing psychosis with inclusion in the study as entry point and last follow-up assessment after 18 months as the end point.

We will use the Mann-Whitney test to examine if people who made a transition scored significantly higher on the CAARMS and the SOFAS compared to patients who did not make a transition. We considered p-values less than 0.05 to be statistically significant.

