A possible strength is the two-stage screening procedure used to detect subjects at risk. Screening the entire help-seeking population referred to community mental health services with a two-stage strategy, can potentially detect more ARMS patients by uncovering at risk cases that would normally never be referred. Many pre-psychotic symptoms are not recognised during the regular referral process. Because we do not want to miss any patients, we probably will not only detect late prodromal patients, but also early prodromal patients. Therefore, this two-stage screening method will detect more ARMS patients than the existing referrals to the specialized clinic, but probably at the expense of more false positives. The referred patients are more likely to be late prodromal than the people recruited by screening. Screening with a highly specific screening tool eliminates most of those not at risk in the first stage. The selected percentage undergoes the second stage of screening with the CAARMS interview. In this enriched sample of (more) psychosis-prone individuals the assessment instruments will probably have a better predictive value. In concordance with previous research [50] we expect about 3.5% of the help-seeking population will have psychotic-like experiences and will have an at-risk mental state. In the selected group we expect the transition rate to be 25 to 35 percent over an 18 month period. If this two-stage screening process proves to be successful, this type of screening could be implemented in routine mental health care.

Another strength of our study is that it has a strong external and internal validity. Since this trial is implemented in a mental health setting, the results will immediately be relevant for clinical practice. All participants receive treatment in a regular outpatient treatment centre in the same way they would have received treatment if they were not enrolled in the study. The internal validity is fine-tuned by supervision of the therapists every two weeks. The researchers and research assistants have supervision every three months. The internal validity is measured by the inter-rater reliability of the CAARMS; the therapy is monitored regularly and reliable and valid instruments are used.

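### The arms are to be compared by an unadjusted chi-square that uses neither the site strata nor the dated follow-up, which leaves the comparison open to bias if drop-out differs by arm

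*Protocol article*

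**What the plan says.** All references are to the protocol article.

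- **Endpoint (Design).** "The main outcome measure is the number of participants who develop florid psychosis within eighteen months".
- **Sizing (Power calculation section).** The planning assumption reads: "We calculated power on an expected transition rate of 35 percent over eighteen months with a 50 percent reduction of transitions in the CBT-group". Sample size is then stated for a "2-tailed test of the proportions with an alpha of .05 and a power of .80 is 2 × 93" per arm. The section expects 30% drop-out over 18 months and plans 240 participants.
- **Allocation (Randomisation).** "Randomisation will be stratified by site, to rule out factors concerning the institutions, therapists and habitat", in permuted blocks of ten within each site.
- **Between-arm test (Analyses).** "Group differences will be analysed by unadjusted chi-square". Comparisons are by intention to treat, missing data are imputed by the EM algorithm, and risk factors are adjusted for only if baseline balance is disturbed. Survival analysis is assigned to time to transition and to risk factors, and the Kaplan-Meier curves are described as exploratory.
- **Abstract.** "Group differences will be analysed with chi-square tests and survival analyses", with no order between the two.
- **Timing (Measurements).** The CAARMS, or its first four scales, is given at months 2, 4, 6, 9, 12, 15 and 18.
- **Differences between sites (Participants, Discussion).** Three regions screen all referrals, and Amsterdam recruits by specialist referral. "The referred patients are more likely to be late prodromal than the people recruited by screening".

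**The concern.** Three design features are not used by the stated test.

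1. Site is a randomisation stratum, and the article itself expects the referral route to bring in patients at a later prodromal stage. The test is nevertheless specified as unadjusted. The conditional adjustment does not repair this: it is triggered by baseline imbalance, site is not among its examples, and site is what blocked randomisation already balances.
2. Transition status is dated at seven assessments, so many of the expected 30% who drop out contribute known event-free time. A chi-square at 18 months can use that time only by assigning such patients an outcome or leaving them out.
3. The Discussion gives the aim as delay or prevention of transition. A comparison of 18-month proportions cannot show delay.

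What is at stake is mainly validity. If drop-out differs by arm, the chi-square can reject a true null hypothesis too often, and the direction of the error depends on how drop-outs are handled. Different retention is plausible, because the Power calculation section offers webcam therapy to the CBT arm. A lesser issue is that the abstract leaves two unranked methods for the same question.

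**Working it through.** **1. The plan's own figure.** For two proportions with pooled variance under the null,

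n per arm = [1.96·√(2·p̄(1−p̄)) + 0.8416·√(p1(1−p1) + p2(1−p2))]² / (p1−p2)².

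- p1 = 0.35, p2 = 0.175, p̄ = 0.2625: n = 98.04, so 99 per arm.
- p2 rounded to 0.17, p̄ = 0.26: n = 92.03, so 93 per arm. This is the stated figure.
- The arcsine formula with 0.17 gives 90.7, so 91. This matches the other stated figure, "2 × 91 for the transition into psychosis".

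The trial is therefore sized for a chi-square-type test of proportions, so the chi-square fits the stated endpoint and sample size.

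**2. Power with equal drop-out.** Simulation assumptions: 240 patients, four sites of 60, blocks of ten, exponential event and drop-out times, events detected at the scheduled visits, 35% against 17.5%. Transitions seen before drop-out are kept. In this table event-free drop-outs count as non-events for the chi-square and Cochran-Mantel-Haenszel (CMH) tests; omitting them changes the chi-square by less than half a point. The first row has 4,000 trials and the others 2,500.

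| Scenario | Chi-square | CMH by site | Log-rank | Site-stratified log-rank |
|---|---|---|---|---|
| No drop-out, equal sites | 87.8% | 87.8% | 87.8% | – |
| 30% drop-out, equal sites | 78.5% | 78.2% | 79.8% | 79.7% |
| 30% drop-out, one site at twice the risk (control risk 56% against 28%) | 80.5% | 81.2% | 81.7% | 83.2% |

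Monte Carlo error at 80% with 2,500 trials is √(0.8·0.2/2500) = 0.8 points. Repeat runs gave 78.6% against 80.7% (unstratified log-rank) and about 79–80% against 81% (stratified) with equal sites. With one site at twice the risk they gave about 80–82% against 84–85%. The gain is about 1 to 3 points, and up to about 5 with the assumed site difference. Site alone (CMH against chi-square) is worth about 1 point. The control risks in the last row average (3·28 + 56)/4 = 35%.

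**3. Type I error with equal drop-out.** With 30% drop-out the chi-square rejects in 4.2% to 5.1% of null trials; the lower values occur when sites differ. Claiming success on either chi-square or log-rank gives 5.4% to 6.2%. The two disagree on significance in about 2% to 3% of null trials and about 5% to 6% under the planned effect.

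**4. Type I error with unequal drop-out (assumed 40% against 20%).** Both arms have a true 18-month risk of 35%. Set λ = −ln(0.65)/18 and μ = −ln(1−d)/18, where d is the drop-out rate. The chance of a detected event is the sum over visits v_k of [exp(−λv_(k−1)) − exp(−λv_k)]·exp(−μv_k):

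- d = 0.40: 26.9%
- d = 0.20: 31.1%

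*Drop-outs counted as non-events.* Spurious difference 4.2 points. SE = √(2·0.290·0.710/120) = 0.0586, so z = 0.72. Rejection = P(Z > 1.24) + P(Z < −2.68) = 11.1%. Simulation: 10.7% to 12.3%. The arm with more drop-out looks better.

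*Event-free drop-outs omitted.* Event-free completers are 0.65·0.60 = 39% and 0.65·0.80 = 52%. The proportions become 26.9/(26.9+39) = 40.8% and 31.1/(31.1+52) = 37.4%, on about 79 and 100 patients. SE = 0.0734, so z = 0.46. Rejection = P(Z > 1.50) + P(Z < −2.42) = 7.5%. Simulation: about 7% to 8%. The arm with more drop-out now looks worse.

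*Log-rank.* Simulated rejection 4.6% to 5.6%. With 3,000 trials the Monte Carlo error at 5% is √(0.05·0.95/3000) = 0.4 points.

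**The case against.** The strongest case for the plan is that a chi-square on a binary 18-month endpoint is a valid test, matches the Design and Power calculation sections, and loses almost no power. Intention to treat and EM imputation are both stated, so the plan does not ignore drop-outs. The Analyses section ties only the chi-square to group differences, so the rivalry between tests rests mainly on one sentence of the abstract. Ranking tests and naming a log-rank or Cox model are often left to an analysis plan, which is not shown.

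Much of this stands, and it rules out several stronger readings that a reader might infer:

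- *That choosing chi-square causes the stated 80% power to be missed.* Not supported. Losing 30% of 240 leaves 84 per arm, below the stated 93, and 84 per arm has 73.6% power at 35% against 17.5%. Any shortfall comes mainly from the allowance for drop-out; the log-rank itself only reaches about 80%.
- *That completers-only power of 73–74% describes the planned analysis.* Not supported. No completers test is proposed, and a transition seen before drop-out is an observed primary event.
- *That ignoring site inflates type I error.* It does not; the test is slightly conservative when sites differ.
- *That two unranked tests seriously inflate error.* The cost is about 1 point, not the 9.75% of two independent tests.

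What does not stand is the appeal to a later document or to EM. The word unadjusted is a stated choice, not an omission. The only reason given for EM is recovery of factor loadings, and nothing says how it would yield a yes/no transition for a patient lost at, say, month 9. Nor is the log-rank free of assumptions: it replaces an imputation assumption with non-informative censoring. If patients leave because they are becoming psychotic, neither method is protected.

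**Conclusion.** The point holds as a recommended change. The stated between-arm test leaves out the site strata and the dated follow-up, and the article does not say whether it or a survival analysis is primary. That the chi-square is primary is an inference from the endpoint, the sizing and the Analyses section.

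In order of importance:

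- **Bias:** type I error of about 7–12% for the chi-square against about 5% for the log-rank, if drop-out is 40% in one arm and 20% in the other. These rates are assumed; the article gives only 30% overall. Multiple imputation or another explicit rule could reduce the bias, but none is fixed for the binary outcome.
- **Power:** about 1 to 3 points, or up to about 5 with an assumed two-fold site risk; nothing without drop-out.
- **Two answers:** about 1 point of type I error if either test counts as success.

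The simulations also assume four equal sites, exponential times and non-informative drop-out.

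**What to change.** Name a single primary analysis: a log-rank test stratified by randomisation site, on all randomised patients, of time from randomisation to first CAARMS-defined transition, censored at the last CAARMS. Report with it a hazard ratio from a site-stratified Cox model and the 18-month Kaplan-Meier risks by arm. Keep a site-stratified (Cochran-Mantel-Haenszel) comparison of 18-month proportions as supportive, and state how outcomes of patients lost before 18 months enter it. Align the abstract and the Analyses section with this order.

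The cost is wording only, since site and all assessment dates are already collected. There are two downsides. The analysis assumes non-informative censoring, so drop-out and its reasons should be reported by arm. The hazard ratio also needs a proportional-hazards check.

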### Intervention

Participants in the control condition will receive treatment as usual (TAU) for the mental problems that they are seeking help for (e.g., depression, ADHD or anxiety disorder). The subjects in the intervention group will receive TAU plus a manualised cognitive behavioural therapy (CBT). The intervention protocol, based on the protocol from the British intervention trial [20,21], is a cognitive behavioural intervention that aims to reduce symptoms, normalises psychosis-like experiences and prevents a catastrophic appraisal of the psychotic-like symptoms from occurring. The idea is that the final common pathway from ARMS to psychosis is largely based on catastrophising the psychotic-like symptoms which are then worsened by a high level of emotional arousal. When the appraisals become fixed and frightening, delusions are formed. The therapy manual in this study is enriched with eight sessions of psycho-education and behavioural experiments with cognitive biases that play a role in the development of delusions and hallucinations. Normalising the odd experiences as a result of perceptual and reasoning biases is supposed to reduce the emotional arousal and over-involvement with the experiences. Catastrophic delusional interpretation of the unsettling experiences is then probably prevented. Behavioural experiments and homework exercises teach people to tolerate psychosis-like experiences and reduce emotional discomfort. The intervention consists of a maximum of 25 sessions within a six-month period. All therapists are psychologists or consultant psychiatrists experienced in CBT with psychotic patients. They are trained in using the protocol and are offered supervision every two weeks during the course of the trial. During the two-hour supervised sessions, audio-taped sessions are discussed and rated on the Cognitive Therapist Scale [25]. Another part of the supervised sessions is dedicated to case formulation and trouble shooting of difficult cases.

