### Measurements

(See also table 4 for measurement moments and instruments)

**Table 4 T4:** measurements

Measurements	T0: baseline	T6: end of the intervention	T12: Follow up	T18: follow up	Transition
CAARMS	X	X	X	X	x

BDI	X	X	X	X	-

SIAS	X	X	X	X	-

EQ5D	x	X	X	X	-

PBIQ-R	x	X	X	X	-

MANSA	x	X	X	X	-

CDS	x			X	x

Verbal Fluency	x	X	X	X	-

Medication check	x	X	X	X	x

Blood sample	x	-	-	-	-

SCAN interview	x	-	-	-	x

PANSS	-	-	-	-	x

PSYRATS	-	-	-	-	x

Treatment check	-	-	-	-	x

CAARMS = Comprehensive Assessment of At Risk Mental State; BDI = Beck Depression Inventory; SIAS = Social Interaction Anxiety Scale; EQ5D = Euroqol-5D; PBIQ-R = Personal Beliefs about Illness Questionnaire-Revised; MANSA = Manchester Short Assessment of Quality of Life; CDS = The Calgary Depression Scale; SCAN = Schedules for Clinical Assessment in Neuropsychiatry; PANSS = Positive and Negative Syndrome Scale; PSYRATS = Psychotic Symptom Rating Scales.

Subjects participate in the study for 18 months. At baseline and at six-month intervals, participants are assessed with the full CAARMS [8]. During these major measurement sessions, participants are also assessed with secondary outcome measures and mediators and moderators. In between the major assessments participants are monitored with a subset of the CAARMS (the first four scales) to assess a possible transition to psychosis. The minor assessments are scheduled at months 2, 4, 9 and 15.

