### Instruments

The following instruments are used:

1. The Prodromal Questionnaire (authorized Dutch translation by [name], [name], [name]) [22] will be used to screen patients for psychosis-proneness in the general help-seeking population and is a 92-item self-reporting lifetime questionnaire, rated on a two point scale ('agree' and 'disagree'.) Of these items, 45 apply in the case of possible sub-clinical positive symptoms. When maximizing the true positive cases, Loewy et al. found a cut-off score of eight symptoms at the positive subscale predictive for an ARMS on the SIPS (a CAARMS look-alike) with a sensitivity of 90% and a specificity of 48% in a population that was referred because of suspected prodromal state [22]. Since we expect more false positives in the general help-seeking population, the cut-off score for the EDIE-screening is higher [26]. Patients are invited for a further structured clinical interview when the total score of positive symptoms exceeds 18.

2. The Comprehensive Assessment of At Risk Mental State (CAARMS [8], authorised Dutch version by [name], [name], [name], [name], [name]) [8] is a semi-structured interview that assesses sub-clinical psychotic symptoms in the last year before assessment. Both intensity and frequency of the symptoms are assessed, in order to dimensionally distinguish between not at risk, ARMS and psychosis (see table 1, 2, 3). The CAARMS has a good reliability. High scores on the CAARMS are predictive for transition into psychosis with a relative risk of 12.44 (95% CI = 1.5 - 103.41, *p *= 0.0025). An ARMS predicts psychosis onset within one year with good sensitivity (86%), specificity (91%), positive predictive value (80%) and negative predictive value (94%) [9,25].

3. Drug and alcohol use are assessed with the Composite International Diagnostic Interview (CIDI) [27]. The CIDI is a comprehensive, fully standardized instrument for assessing mental disorders according to the definitions and criteria of ICD-10 and DSM-IV. Good reliability and validity of the CIDI have been reported with all Kappa coefficients above .5 for reliability and above .7 for validity [28].

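### The symptom analysis pairs ANCOVA with single EM filling and fixes no visit, though the four CAARMS scales are rated at seven follow-ups; one mixed model with a named lead contrast should replace it

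*Protocol article*

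**What the plan says.** The Analyses section gives one method for symptom severity: for the "effects of CBT on the positive symptoms reported on the first four scales of the CAARMS, analysis of co-variance will be used". It states no visit, covariate or summary over visits. For incomplete data the same section says "Missing data will be imputed by EM-algorithm", and it asks for intention-to-treat comparisons.

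The Measurements section sets the schedule. "At baseline and at six-month intervals, participants are assessed with the full CAARMS", which gives months 6, 12 and 18 after baseline. Between these visits patients are "monitored with a subset of the CAARMS (the first four scales) to assess a possible transition to psychosis", and "The minor assessments are scheduled at months 2, 4, 9 and 15". The outcome of the ANCOVA is therefore rated at 3 + 4 = 7 follow-ups.

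Two other statements bear on which visits can be averaged. The Intervention section says "The intervention consists of a maximum of 25 sessions within a six-month period". The Instruments section describes the CAARMS as a "semi-structured interview that assesses sub-clinical psychotic symptoms in the last year before assessment".

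**The concern.** ANCOVA in its ordinary form has one outcome value per patient. Applied to this schedule, it either analyses one visit and leaves six ratings unused as outcomes, or it is repeated by visit and scale. Four scales at three major visits would give 12 results with no lead one.

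The Power calculation section expects 30% drop-out over 18 months, so a month-18 analysis depends heavily on how gaps are filled. Single filling by EM gives each absent patient a predicted value, and the ANCOVA then treats that value as if it had been measured. Both the precision of the symptom result and the honesty of its p-value are at stake.

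**Working it through.** **Inputs from the article.** Seven follow-up ratings of the four scales, 30% drop-out by month 18, 240 patients (120 per arm), EM imputation. The article gives no SD, between-visit correlation or power for this ANCOVA, so it has no figure of its own to reproduce.

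**Assumptions.** Between-visit correlation ρ either equal (0.3 to 0.9) or decaying with time (six-month value 0.5 to 0.9). Drop-out is linear in time and permanent, so the fraction seen at month t is 1 − 0.30·t/18: 90% at month 6, 80% at month 12, 70% at month 18.

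**Step 1: complete data, equal correlation.** In units of the outcome variance, adjusted for baseline:
- one follow-up: 1 − ρ²
- mean of r follow-ups: (1 + (r − 1)ρ)/r − ρ²
- ratio: (1/r + ρ)/(1 + ρ)

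For r = 7 the ratio is 0.341 at ρ = 0.3, 0.429 at 0.5, 0.496 at 0.7 and 0.549 at 0.9. It equals one half at ρ = 1 − 2/7 = 0.714. For r = 3 it runs from 0.487 (ρ = 0.3) to 0.649 (ρ = 0.9) and equals one half at ρ = 1/3.

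**Step 2: with drop-out.** The comparator is a month-18 ANCOVA in completers, with variance (1 − ρ₁₈²)/0.70, where ρ₁₈ is the baseline to month-18 correlation. For the mixed model with free arm-by-visit effects, the information is the sum over drop-out patterns of (fraction with that pattern) × (inverse baseline-adjusted covariance of the visits seen). Its inverse, V, gives w′Vw for a contrast w. Variance relative to the comparator:

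| Correlation | Month-18 contrast, all seven visits used | Average of months 6, 12, 18 (those visits only) | Average of all seven |
|---|---|---|---|
| equal 0.3 | 0.967 | 0.416 | 0.268 |
| equal 0.5 | 0.941 | 0.468 | 0.332 |
| equal 0.7 | 0.920 | 0.506 | 0.379 |
| equal 0.9 | 0.902 | 0.537 | 0.417 |
| decaying 0.5 | 0.944 | 0.453 | 0.316 |
| decaying 0.7 | 0.909 | 0.466 | 0.318 |
| decaying 0.9 | 0.872 | 0.445 | 0.292 |

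Letting the other four visits inform the three-visit average changes little (0.41 to 0.52).

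**Step 3: against a month-6 ANCOVA (90% seen).** The seven-visit average has a ratio of 0.35 to 0.54 under equal correlation and 0.53 to 0.93 under decaying correlation. The average of months 6, 12 and 18 has 0.54 to 0.69 under equal correlation. Under decaying correlation it runs from 0.76 to above 1, because later visits are less well predicted by baseline and have more drop-out.

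**Step 4: ANCOVA on EM-filled values.** Simulation with no true effect, 120 per arm, the same drop-out (at random), a month-18 ANCOVA and a nominal 5% level; 800 runs in each of five correlation settings (equal 0.3, 0.5, 0.7; decaying 0.6, 0.8).
- Arm in the imputation model: false-positive rate 12.5 to 14.8% (Monte Carlo error about √(0.13 × 0.87/800) = 1.2 points). A two-sided rate of 13.8% corresponds to a critical value of 1.485 instead of 1.96, so the reported standard error is about 1.485/1.96 = 0.76 of the true one.
- Arm left out: the rate stays near nominal (3.6 to 5.5%), but drop-outs then carry a treatment difference only through their earlier ratings, so a real effect is pulled towards zero.

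The article does not say which form is meant.

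**Step 5: which visits can lead.** Months 2 and 4 lie inside the six-month therapy period. If the one-year recall window also applies at follow-up, the month-2 rating reaches 12 − 2 = 10 months before randomisation, month 4 reaches 8, month 6 reaches 6 and month 9 reaches 3. Only months 12, 15 and 18 look back entirely after it.

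**The case against.** The strongest reply is that ANCOVA is a valid method for a randomised comparison, that it can be run on the mean of several follow-ups, and that a condensed article may leave the choice of visit to the analysis plan. That stands. The silence on visit is not in itself the defect, and one value per patient is the usual reading of ANCOVA, not a statement in the article.

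A reader might infer that the plan certainly throws away more than half of the available precision. The documents do not support that:
- They give no correlation. With complete data and equal correlation, the variance loss drops below half once ρ exceeds 0.714, and overlapping recall windows make high correlation plausible.
- On the standard-error scale the loss with complete data is under half throughout (26 to 47% for ρ from 0.9 to 0.2).
- Most of the gain comes from changing the question from one visit to an average.
- Against a month-6 ANCOVA it can shrink to about 7% for the seven-visit average.
- The completer comparator is not the plan's own handling, which is EM filling.

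Two further points stand. The minor visits exist to detect transition, so not using them as efficacy outcomes is defensible. And the persistence aim is framed as a number of patients and sized by a test of proportions (2 × 82), so this ANCOVA is not its sized test.

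What the reply does not answer is single EM filling. EM can draw on earlier ratings, but an ANCOVA on the filled values either overstates certainty or dilutes the effect.

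**Conclusion.** The point holds in limited form. The method as worded suits a seven-visit outcome with 30% expected drop-out poorly, and its pairing with single EM filling does not give trustworthy standard errors.

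- **Validity:** a false-positive rate of roughly 12 to 15% instead of 5% if arm is in the imputation model; a diluted effect if it is not.
- **Precision at month 18:** a modest gain, with variance 3 to 13% lower than a completer ANCOVA.
- **Precision for an average:** variance about 0.42 to 0.54 of that comparator for months 6, 12 and 18, and 0.27 to 0.42 for all seven visits, but these answer a different question.

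The sizes rest on assumed correlations and linear drop-out, and the false-positive rate also on drop-out at random. The seven-visit average should not lead, because it mixes in visits during therapy and symptoms that may predate randomisation.

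**What to change.** Replace the ANCOVA by one likelihood-based repeated-measures mixed model on the summed score of the four scales at months 2, 4, 6, 9, 12, 15 and 18, with visit, arm, arm-by-visit, baseline score and site. Fit it to the observed ratings, without EM filling.

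Pre-specify one lead contrast at the major visits, for example month 18 or the average of months 6, 12 and 18. Report the seven-visit average as supportive only.

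The cost is analysis wording: no new data or visits. There is a small downside. An averaged contrast answers a different question from a single-visit one, so the single-visit contrasts must be shown beside it. The model also assumes that drop-out is explained by the ratings already observed, which should be stated.
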